## **Abstract**

**Design and objective:** This randomized controlled study aims to evaluate an intervention in Malaysia that educates women about breast cancer (BC) screening and navigates them to Clinical Breast Examination (CBE) services and leads to an increase in BC screening uptake whilst taking account of the COVID-19 pandemic context.

**Study population:** Women who are aged 40-74 years, living in Segamat District, Malaysia, with a registered mobile phone number will be sampled randomly from the total population of women who participated in the South East Asian Community Observatory (SEACO) Health Survey (2018). BC patients or women experiencing BC symptoms at the time of recruitment will be excluded. Computer-generated random numbers will be used to assign women randomly to the intervention group (IG) or the comparator group (CG).

**Interventions:** The IG will receive a multi-component mHealth intervention i.e. information about BC will be provided through an educational website, and telephone calls and text messages from community health workers (CHWs) will raise BC awareness and offer to navigate women to CBE services. The usual free opportunistic screening service will be available for CG participants. It will not be possible to 'blind' participants, data collectors and CHWs.

**Outcome measures:** CBE screening uptake is the primary outcome measure and will be recorded by nurses conducting CBEs. Data collectors will use telephone interviews to assess differences in relation to awareness about BC signs/symptoms, intention to attend CBE and mammogram screening, breast self-examination practice and barriers to screening pre- and post-intervention. IG participants will provide an assessment of intervention acceptability and appropriateness.

**Analysis:** A Chi-square test will be used to compare the proportion of participants who attended CBE within 4-6 weeks after the baseline survey in the IG and CG. Multivariate regression analyses will be conducted to investigate between-group differences over time and variable influences on screening participation.

## Background

Breast cancer (BC) is the most common cancer in Malaysia with an age-standardized incidence rate (ASR) of 34.1/100,000 (2012-2016) [1] and an age-standardised mortality rate of 12.0/100,000 (2020) [2]. Prior to the COVID-19 pandemic, it was estimated that 1 in 10 males and 1 in 9 females will develop cancer before 75 years old [1] and that about one-third to one-half of cancer-related deaths could be avoided through early presentation, detection and appropriate treatment. BC patients were diagnosed at advanced stages (48%) [1] with a considerable variation in BC incidence and prognosis across ethnic groups and geographical areas in Malaysia. For example, although BC incidence was lowest among ethnic Malay women [1], late presentation and poorer survival was more prevalent among this ethnic group compared to others [3]. Women from rural areas also presented at later stages, i.e. the majority (60%) of BC patients from rural areas of Segamat district presented at stages III and IV [4].

According to the World Health Organization (WHO), early detection, treatment and management of BC are the three pillars of BC control [5,6]. Health promotion and early detection are key in LMICs where late-stage detection of BC is high [6]. The most common screening modalities are clinical breast examination (CBE) and mammogram. CBE is less cost-intensive than mammograms and evidence suggests that CBEs are as effective as mammograms in terms of mortality [7]. In Malaysia, opportunistic CBE and mammography are the two main methods of BC screening [8]. Consequently, BC screening uptake depends on doctors offering CBE and mammogram when women at average risk of BC attend the clinic and/or women being aware of BC and the importance of screening and early detection.

CBE uptake in Malaysia varies between the main ethnic groups (Malay, Chinese, Indian and indigenous women) and ranges from 37% among indigenous women to 66% among Chinese Malaysians [9]. A recent survey of 993 women in Selangor State showed that only 29.7% of study participants aged  $\geq 50$  years attended BC screening [10]. A quarter of the sample did not know 'how to go about BC screening', understanding about mammograms was lacking and willingness to participate in BC screening was low [10]. Negative beliefs and attitudes towards cancer and screening, lack of time and confidence to visit a doctor were also common barriers to help-seeking [10].

Lack of awareness about cancer signs is one of the key risk factors for patient-related delay in receiving a diagnosis [11,12], and difficulty in accessing a doctor was previously associated with anticipated delayed help-seeking for breast changes [12]. These factors may help to explain why BC patients in poor rural communities in Malaysia tend to be diagnosed at advanced symptom presentation [4]. Thus, providing easy-to-understand education and addressing access barriers is key in improving cancer screening uptake. Often, community health workers (CHW) are trained to engage with communities in low- and middle-income countries (LMICs) where resources are limited and commonly play a role in educating and assisting individuals to access health services [13,14] For example, a recent review

highlighted the role that CHWs play in promoting cervical cancer screening [13] and, in the response to the COVID-19 pandemic, CHWs have delivered testing and vaccination programmes in collaboration with local authorities, particularly in LMICs with less resourced health care systems [15].

The COVID-19 pandemic and the resulting movement control orders (MCOs) in Malaysia, which enforced travel restrictions to limit the spread of the virus, add further barriers to accessing health services, particularly amongst rural communities, and contribute potentially to an increase in BC cases and their late detection. Globally, the pandemic is increasing the use of mobile health (mHealth) and telehealth for the management of the pandemic and the delivery of healthcare [16–18]. The WHO supports the adoption of a ‘global strategy on digital health’ [19] to contribute to the advancement of the sustainable development goals [20]. Digital health is also likely to aid in the task of navigating at-risk individuals to use cancer screening services [21,22]. Our main aim is to design, implement and evaluate an intervention to improve uptake of CBE screening in Malaysia and BC symptom recognition in the context of the COVID-19 pandemic.

### **Conceptual and theoretical framework**

In keeping with the UK MRC Framework for the Development and Evaluation of Complex Interventions [23], we conducted a series of research activities before preparing this protocol for a RCT of the intervention. We reviewed and synthesised evidence and experiential learning regarding the implementation of community navigation and mHealth education programmes for BC early detection and diagnosis in LMICs; assessed the views and preferences of key stakeholder groups regarding community navigation, specifically the views of women in rural communities; and co-designed a culturally sensitive education and navigation programme for Malaysia. These investigative activities and results are outlined below in terms of informing the protocol for our RCT study.

The evidence synthesis that informed the intervention design was informed by a rapid review of reviews, quantitative surveying of the target population about their BC screening practices and qualitative interviews and focus group discussions (FGDs) with the target population and key stakeholders. The Behaviour Change Wheel (BCW), a theoretical framework that is used widely to guide the design of behavior change interventions, including interventions to improve early cancer diagnosis [24,25], was applied to the intervention design process [26]. We mapped the results from the evidence synthesis (e.g. facilitators and opportunities) onto the COM-B (Capability, Motivation and Opportunity – Behaviour) [27] core of the BCW (**Table 1**) to inform the development of the intervention.

### *Rapid review of reviews*

The rapid review of reviews assessed the implementation and effectiveness of mHealth interventions to increase awareness about cancer screening and screening uptake [28]. Text messages and phone calls were the most commonly utilized mHealth methods to contact prospective participants. However, the overview indicated that text messages or email alone were ineffective in increasing screening uptake. Successful cancer screening uptake interventions combined at least two modes of communication, facilitated or offered screening appointments for participants, alone or in combination with education, patient navigation and/or addressed negative beliefs of participants (similar to findings from recent review of CRC screening uptake in LMICs [29]). The overview identified also a lack of navigation in cancer service delivery and a need to improve two-way communication between patient and service provider. Text message reminders, too, enhanced screening uptake. Conversely, research about mHealth interventions in vulnerable populations was sparse.

### *Qualitative research*

We conducted four FGDs with 22 women from the major ethnic groups in Malaysia and interviews with 22 key stakeholders including nurses, doctors, radiologists and volunteers from the Breast Cancer Support Society Segamat. The qualitative research explored attitudes, barriers and beliefs about BC screening, challenges in breast health service delivery and how gaps in BC screening and early diagnosis in rural Malaysia might be addressed. A lack of resources (e.g. female radiographers and doctors, equipment, subsidized mammograms, and private CBE/mammogram facilities) was noted to be a challenge for primary and secondary care services. Often, screening programmes targeted women who attended mother-child clinics rather than at-risk women. Community-related challenges included lack of knowledge about BC and screening, preferential trust in traditional medicine, lack of support from husbands and fear of marital separation, apprehensions about diagnosis and treatment (breast removal), embarrassment about breast-related issues and travel distance to screening facilities. Participants recognized the importance of educating women to address the fear and embarrassment about screening and BC and to highlight the importance of early detection. Additional noted supports included subsidized screening, health talks and/or support groups for women and the involvement of non-governmental organizations.

### *Quantitative research*

In 2017, we run a survey of 250 women aged 40 years and above, who were randomly sampled to represent women from Segamat district, which confirmed low screening awareness and uptake [30]. Only 53% and 47% of women heard of CBE and mammogram, respectively, and 36% and 22% received

the respective screening test. Half of the sample endorsed CBE (50%) and mammogram (44%) as beneficial and only 46% were aware that their nearest clinic offered CBE screening. The majority of participants lived less than 30 minutes away from clinics that facilitated CBE screening (74%) though only 26% lived near a mammogram facility. Barriers to attending BC screening were stigma, fears related to diagnosis and surgery, breast examination by a male doctor, delay in getting an appointment, cost of screening and distance to healthcare facility. There were major differences between ethnic groups, e.g. significantly more Malays reported perceived barriers compared to other ethnic groups (i.e. fear of diagnosis, lack of family support, lack of time, cost of screening, distance to health clinic and fear of pain and discomfort).

## **Study design and methods**

This section presents the intervention and the plan for the implementation of the randomised study and outcome measures that will be used to evaluate the intervention.

### **Setting**

Malaysia is a multi-ethnic country with a population of 32.7 million in 2020 [31]. The main ethnic groups are Malays (69.6%), Chinese (22.6%) and Indians (6.8%) [31] and the majority of the population (77%) live in urban areas and 23% live in rural areas [32]. The South East Asian Community Observatory (SEACO) is a health and demographic surveillance system (HDSS) established in 2011 by Monash University and is located in Segamat, a district in the state of Johor, Peninsular Malaysia. SEACO has a comprehensive database of over 44,000 people living in Segamat, Malaysia, which is 85% of the population in 5/11 sub-districts (Sungai Segamat, Jabi, Gemereh, Bekok, and Chaah) and 24% of the total population in Segamat. It captures detailed longitudinal information about the health of Segamat residents; and provides a research platform for a focused study of screening implementation [33]. Participants will be recruited from two sub-districts, i.e. Sungai Segamat – a town area, and Jabi – a rural area, which contain a mix of ethnic groups, and are representative of the population in Segamat. SEACO conducts three main types of surveys: 1) An annual survey to collect a range of demographic indicators 2) a full census survey, conducted every 5 years, that includes a more detailed questionnaire than the annual survey and 3) a health survey, conducted every 5 years, to examine the health profile of those aged  $\geq 35$  years regarding illness, health services use, mental health, quality of life etc.

### **Study population**

The target population are residents from Sungai Segamat and Jabi who completed the health survey in 2018, are recorded in the SEACO database and have previously given consent to be contacted about participating in research studies. We will contact women aged 40-74 years who have registered a phone number with SEACO. Only women who will be able to provide a mobile phone number when contacted will be able to participate in the study. BC patients and survivors will be excluded from this study. Women who report to the researchers at the time of the interview that they are experiencing BC symptoms will be excluded from the research and encouraged to seek help from their local doctor as soon as possible.

### **Participant randomization and recruitment**

Women will be selected randomly from the two sub-districts using the SEACO database as the sampling frame and then randomized to the intervention group (IG) or comparator group (CG) with a 1:1 allocation prior to being contacted. Randomisation will be conducted by a SEACO statistician ([name]) using Stata module RANDOMIZE without blocks [34]. Participant enrolment will be conducted by trained SEACO data collectors. All randomly sampled women who were then randomized to the IG or CG will be invited to participate by trained data collectors over the phone. The resources for this study do not permit separation of enrollment and data collection procedures and, so, DCs will be aware which group the women are assigned to and this aspect may increase the risk of bias. Participants and intervention providers will not be blinded during the enrollment and surveys. CHWs will not collect outcome measures. Women who agree to participate will receive an explanatory statement about the study and a token of appreciation for their participation.

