### *Intervention Group*

**Figure 1** demonstrates the intervention flow. Trained data collectors from SEACO will recruit women assigned to the IG via phone call and conduct a baseline survey with women who provide verbal consent to participate in the study. Data collectors will then send women from the IG group a text message that contains the link to the BCAC materials [36]. One CHW will be assigned to support between 50-60 women who agreed to participate. CHWs will call the women they have been assigned to in the same week to discuss BC symptoms and BSE, address any barriers to screening, and ask them whether they are interested in attending a CBE at the LPPKN clinic. If the participants are interested, CBE appointments will be offered to take place the following week at a time that suits the participant. CHW will address concerns of participants who are not interested in screening, but no further action will be taken by the CHW if participants refuse to attend the CBE. Nurses will ask women with normal CBE results to attend screening biannually as recommended in the clinical practice guidelines [37]. Women with abnormal findings during the CBE will see a doctor at the LPPKN clinic who will refer them to a hospital for a mammogram as soon as possible after their CBE, free of charge. Participants will be informed in private about their mammogram results by the LPPKN nurses and CHWs will not be informed of the result. CHWs will call women who do not attend the CBE to identify the reason for non-participation, address further barriers and reschedule the appointment if agreed with the participant. CBE positive women who miss their mammogram appointment will be called by the LPPKN nurses.

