### *Comparator Group*

During the recruitment call, participants from the CG will be made aware that BC is the commonest cancer amongst women in Malaysia and about the importance of early detection. Women who will be randomized to the CG will not receive the intervention but may avail of 'usual' screening via their local clinic (subject to pandemic restrictions).

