### *Sampling size and procedure*

Women from Sungai Segamat and Jabi will be randomized to either IG (n=466) or CG (n=466) prior to recruitment. A sample of 1600 women (n=800 for the IG and CG) will be drawn from the SEACO database to account for participants who are not interested in participating. A sample size of 932 will allow 80% power to detect, as statistically significant at the 5% level, an increase of 9% or more in the proportion aware of a BC symptom in the IG compared to the CG after the intervention (based upon baseline awareness of a breast lump as a cancer symptom of 65% from our previous Newton-Ungku-Omar funded study). The sample size of 932 will also allow 80% power to detect an absolute increase in the proportion of women who avail of a CBE following receipt of the intervention of the intervention of 9% compared with the comparator group. The pilot will be tested with 40-50 participants.

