**Train 1-2 male CHWs**

Male CHWs will be trained to provide information for women's husbands/ partners /other male relatives who the women rely on for transport and support.

**CG: Telephone recruitment & baseline survey** (n=466)

SEACO staff will assess and recruit randomly selected women (provide study information, assess eligibility, gain verbal consent, complete baseline survey)

**IG: Telephone recruitment & baseline survey** (n=466)

SEACO staff will assess and recruit women randomized to the intervention group (provide study information, assess eligibility, gain verbal consent, complete baseline survey)

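### Recruiters know each woman's arm before eligibility check, consent and baseline survey, so losses among allocated women can depend on arm and bias the CBE comparison

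*Protocol*

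**What the plan says.** The Protocol section on participant randomization and recruitment sets the order. Women are sampled, "then randomized to the intervention group (IG) or comparator group (CG) with a 1:1 allocation prior to being contacted". Next, "Participant enrolment will be conducted by trained SEACO data collectors". The section gives limited resources as the reason why enrolment and data collection are not separated, and concludes that "DCs will be aware which group the women are assigned to and this aspect may increase the risk of bias". It adds: "Participants and intervention providers will not be blinded during the enrollment and surveys".

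The other sections keep this order:

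- Intervention Group: "Trained data collectors from SEACO will recruit women assigned to the IG via phone call and conduct a baseline survey". The text message with the link to the education materials is sent after that survey, and the community health worker (CHW) call follows.
- Figure 1, IG recruitment box: "SEACO staff will assess and recruit women randomized to the intervention group (provide study information, assess eligibility, gain verbal consent, complete baseline survey". The CG box lists the same steps.
- Study population: women who report breast cancer symptoms at the interview are excluded, so this exclusion is also applied on the call.
- Comparator Group: "During the recruitment call, participants from the CG will be made aware that BC is the commonest cancer amongst women in Malaysia", together with the importance of early detection.
- Sampling size and procedure: 466 per arm are randomised before recruitment, yet "A sample of 1600 women (n=800 for the IG and CG) will be drawn from the SEACO database" to allow for women who are not interested. The randomization section says that all randomised women are invited.
- Statistical analysis: the chi-square test compares the proportions of IG and CG participants who attended CBE.

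**The concern.** Randomisation makes two groups comparable at the moment of allocation. Here the groups that are compared form later, after refusals and exclusions on a call during which the recruiter knows the arm and the woman is not blinded to it. If willingness to enrol, or the way eligibility is probed, differs between arms, the enrolled groups can differ in their inclination to be screened. That inclination also drives the primary outcome. Equal numbers of 466 per arm would not show the problem.

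The baseline survey is affected too. Awareness, intention and barriers are asked by interviewers who know the arm, so the starting point for the secondary change measures is not protected.

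**Working it through.** **1. The plan's own sample size.** Using the two-proportion formula with pooled variance under the null, two-sided 5% (sidedness is not stated, so this is assumed), 80% power and 1:1 allocation:

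n = [1.960 × √(2p̄(1−p̄)) + 0.842 × √(p₁(1−p₁) + p₂(1−p₂))]² / (p₂−p₁)²

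With p₁ = 0.36 and p₂ = 0.45: p̄ = 0.405, and (1.3607 + 0.5818)² / 0.0081 = 465.8, so 466 per arm and 932 in total. The 36% is the share who had received a CBE in the team's earlier survey (Quantitative research section). The sample-size section does not name it as the input. The target of 466 is therefore reproducible and is not in dispute.

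**2. Room for loss after allocation.** 466/800 = 58.25% need to enrol. Up to 800 − 466 = 334 per arm, or 41.75%, may be lost between allocation and baseline.

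**3. How much bias could follow.** The protocol gives no arm-specific refusal rates and no background CBE uptake over the 4 to 6 week window. All rates below are assumptions, and there is no true effect. Women are of two types, inclined to screening or not. The spurious difference is

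(inclined share in IG − inclined share in CG) × (uptake if inclined − uptake if not).

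*Set A.* Half the pool is inclined and consents at 75% in both arms. The others consent at 41.5% in CG and 30% in IG.

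- CG consent: 0.5 × 0.75 + 0.5 × 0.415 = 58.25%. Inclined share: 0.375/0.5825 = 64.4%.
- IG consent: 0.5 × 0.75 + 0.5 × 0.30 = 52.5%. Inclined share: 0.375/0.525 = 71.4%.
- Difference in share: 7.0 points.
- Uptake 60% v 10%: 7.0 × 0.50 = 3.5 points. Uptake 20% v 2%: 7.0 × 0.18 = 1.3 points. Uptake 10% v 1%: 7.0 × 0.09 = 0.6 points.

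Set A yields only 0.525 × 800 = 420 IG women, short of 466, so a second set holds enrolment at 466 in both arms.

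*Set B.* CG enrolment is unselective, so its inclined share is π. IG enrolment favours inclined women by an odds ratio (OR). Their consent q₁ and the others' consent q₀ satisfy πq₁ + (1−π)q₀ = 0.5825, and the IG inclined share is πq₁/0.5825. Four of the cases run, including the two extremes:

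| π | OR | q₁, q₀ | IG share | Uptake inclined v not | Spurious difference | Chance of p < 0.05 |
|---|---|---|---|---|---|---|
| 0.36 | 1.5 | 0.645, 0.547 | 0.398 | 30% v 5% | 1.0 points | 7% |
| 0.36 | 2 | 0.687, 0.524 | 0.425 | 50% v 5% | 2.9 points | 19% |
| 0.50 | 2 | 0.666, 0.499 | 0.572 | 50% v 10% | 2.9 points | 16% |
| 0.50 | 3 | 0.713, 0.452 | 0.612 | 50% v 5% | 5.0 points | 39% |

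The last column uses 466 per arm. In the bottom row, CG uptake is 27.5% and IG uptake 32.5%, the standard error is √[(0.275 × 0.725 + 0.325 × 0.675)/466] = 0.030, and 1 − Φ(1.96 − 0.0502/0.030) is about 0.39.

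**4. Is knowledge of the arm needed on the call?** The text link follows the baseline survey, and CHWs are assigned to women who have already agreed to take part. The only arm-labelled content before baseline is the statement that the Comparator Group section specifies for the CG. If that statement goes to everyone, nothing described on the recruitment call depends on the arm. One person can enrol and interview without holding the allocation.

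**The case against.** The best defence has three parts.

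*The risk is disclosed.* The protocol says that data collectors know the arm, gives a reason and admits possible bias. That is candid, but no safeguard is stated. Nurse-recorded CBE attendance, with CHWs collecting no outcomes, limits bias in measuring the outcome. It does nothing about who enters each group.

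*Much of the loss may be harmless.* The 800 is an allowance for women who are not interested. Women who have no mobile number or cannot be reached are unlikely to be lost differently by arm. This stands: 42% is a ceiling on the loss after allocation, not an estimate of arm-dependent loss.

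*Concealment has a price.* A fuller common description could tell CG women about navigation and free CBE, prompt some to be screened and dilute the contrast. This also stands and limits how the script should be written.

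A reader might also infer more than the text supports:

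- That recruitment continues until 466 per arm agree. No such stopping rule is stated, and all randomised women are to be invited.
- That IG women are asked to accept CHW calls and a CBE offer while CG women are asked only for surveys. Figure 1 lists the same steps for both arms, and the CBE offer comes in the later CHW call.
- That the breast cancer facts are withheld from IG women. They are specified for the CG, but no section says that the IG does not hear them.
- That uptake in the IG is inflated by a third or more of the 9-point target. That rests on one assumed scenario (3.5 points) that also misses the enrolment target. Nothing shows that screening-averse women refuse the IG more often.

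**Conclusion.** The concern holds as a flaw in allocation concealment. The protocol itself states that eligibility, consent and baseline follow an allocation known to the recruiter, and it leaves room for up to 334 of 800 women per arm to be lost at that stage. Only the arm-dependent part of this loss biases the primary comparison. The size and direction of the bias cannot be derived from the protocol. Under the assumed rates above, the spurious difference is about 0.6 to 5 points against a 9-point target. It would be nil if losses did not depend on arm, and would reverse if inclined women were less likely to enrol in the IG than in the CG.

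The stated resource limit explains why one person does both tasks. It does not require that person to know the arm beforehand.

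The analysis set may be defined in an analysis plan not shown, but that would not settle the matter. Among enrolled women, later analysis cannot be relied on to undo selection on motivation. Analysing all 800 allocated per arm would preserve the randomisation at a possible cost in power. If the 9-point effect occurred only in the 58.25% who enrol, the difference would be 0.09 × 0.5825 = 5.2 points. Power would then be 57.7% at an assumed comparator rate of 36%, 70.8% at 20% and 88.5% at 10%. The remedy therefore has to be in place before recruitment starts.

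**What to change.** - The SEACO statistician generates and holds the allocation list. Data collectors work from one mixed, unlabelled call list.
- Both groups get the same neutral study information, including the breast cancer statement that the Comparator Group section specifies for the CG. The navigation offer is described no further than consent requires.
- Each woman's allocation is released only after eligibility, consent and baseline survey are complete. The IG text link is then sent. Refusal and exclusion cannot depend on an arm that neither party knows, so the enrolled groups remain randomised groups and the target stays at 466 per arm.
- Compare all women who complete baseline in the group to which they were allocated.
- Reconcile the sample-size section and Figure 1 with the randomization section: 800 per arm allocated under concealment, all invited, with a recruitment target of 466 per arm.

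Cost: a change to the call script and list handling, and an ethics amendment, with no added staff or calls. The common description may slightly raise awareness or screening in the CG, which would dilute the contrast, so its wording should be kept short.
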